#### Recruitment strategies

This study will establish recruitment centers in two metropolitan districts: Islamabad and Rawalpindi. Participants will be enrolled based on their eligibility criteria through local mobilization. An ARI expert will conduct screening interviews. Through this independent and robust recruitment strategy, the study will achieve the required sample size. Face-to-face adherence reminder sessions will be held during the initial recruitment and at each subsequent study visit. These sessions will cover the following:Emphasizing the significance of adhering to study guidelines for the daily usage of productsProviding instructions regarding the consumption of study products, such as proper dosage timing, storage guidelines, and the importance of taking the prescribed dose as a wholeFollow-up sessions will take place during subsequent visits. Participants will be inquired about any difficulties they might be experiencing in adhering to their study interventions. These sessions will involve a brief discussion on the reasons behind missed doses and will offer simple strategies to enhance adherence.

### Study design

After the screening of the participants, this study will conduct a baseline survey to evaluate smoking status, smoking behavior, sociodemographic characteristics, health status, economic barriers, and motivation to stop smoking before the intervention and try to make a balance randomization between the control and the treatment groups. After completing the baseline survey, the three-arm study design would randomize 600 participants into three groups.E-cigarette: The 200 participants will receive e-cigarettes along with basic care counselling.Nicotine pouches: The 200 participants will receive nicotine pouches along with basic care counselling.Basic care counselling: The 200 participants will receive basic care counselling.

Four basic care counselling sessions will be held over the course of 48 weeks with the supply of e-cigarettes and nicotine pouches. These e-cigarettes and nicotine pouches will be provided in line with the indicated tastes and flavors. Every 12 weeks, a standard care counselling session will be offered, followed by a study visit to track any alterations in the user’s physical or mental health as well as any side effects from using nicotine pouches or e-cigarettes. All participants will complete a follow-up survey at 60 weeks. However, the provision of e-cigarettes and nicotine pouches will be stopped after the first 48 weeks.

The remaining 12 weeks will be followed without providing any e-cigarettes or nicotine pouches. The participants must buy these items on their own. The overall five follow-ups will be conducted over the course of 60 weeks. Of these, four follow-ups will be during the period in which the participants received interventions, and one follow-up will be post-intervention period of 48 weeks. Additionally, a flowchart depicting the unified requirements of reporting trial is shown in Figs. 1 and 2 along with the explanation of the participants’ research schedule.

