#### Secondary outcomes

Secondary outcomes will include 7-day point-prevalence abstinence (at all subsequent checkups; biochemically validated at weeks 12, 24, 36, 48, and 60). As a secondary goal, this study will analyze the harm-reduction effect of e-cigarettes and nicotine pouches, as well as the analysis of adverse events.

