### Statistical analysis

To provide a summary position of the important variables of the population under clinical trial, a univariate analysis will be employed for data analysis and reporting. To examine the cross-relationship and association between selected variables, bivariate analysis and cross tabs will be used. Univariate data analysis is relevant and provides easy to understand information for focusing on a given variable at a time. The bivariate data analysis is helpful in examining the relationship and association between selected variables based on the understanding from previous studies or the theory. The differences in intervention indicators between the control and the treatment groups will be evaluated with the simple *t*-test and variance analysis.

The information obtained from the baseline survey will help in the planning (refine targeting, indicators to monitor), recommendations toward study design, implementation, and fine-tuning of the intervention objectives, backed by evidence-based research. However, the real execution of true experiment in the field is almost impossible due to heterogeneity of the beneficiaries. Therefore, we propose an alternate but similar approach, i.e., quasi-experimental difference in difference (DID) design, which is a close form of experimental research, widely used in the social sciences. The second-best option would be propensity score matching (PMS) technique to estimate the average treatment effect of the interventions.

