### Data handling, monitoring, and recordkeeping

#### Survey instrument

In the clinical trial, structured questionnaires will gather data on respondent socioeconomic status, combustible smoking usage, intervention use, health status, and side effects of intervention products, etc. All essential topics will have clear definitions included in the questionnaire so that the interviewer can refer to them as and when needed. The questionnaire, translated into the local language of Urdu, will have instructional comments. Each question will be carefully reviewed to ensure elimination of leading or biased questions. On the Android-based census and survey processing system (CSpro) application, data will be gathered. Tablets using the Android operating system will be connected to a local server to guarantee security and data consistency. The program will allow users to save all collected data offline.

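### Adverse events are described only as side effects of the two products, so a comparison with the counselling arm risks unequal ascertainment

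*Protocol article*

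**What the plan says.** Under Secondary outcomes, the article adds a harm-reduction analysis "as well as the analysis of adverse events". It gives no definition of an event and no method specific to events.

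Two places describe collection:

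- **Study design.** "Every 12 weeks, a standard care counselling session will be offered, followed by a study visit". That visit has two purposes. One is "a study visit to track any alterations in the" physical or mental health of the person, who is called the user. The other is to record "any side effects from using nicotine pouches or e-cigarettes".
- **Survey instrument.** The structured questionnaires cover, among other topics, "intervention use, health status, and side effects of intervention products, etc".

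Health is also recorded before randomisation: "this study will conduct a baseline survey to evaluate smoking status, smoking behavior, sociodemographic characteristics, health status" and further topics.

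On analysis, Statistical analysis states: "The differences in intervention indicators between the control and the treatment groups will be evaluated with the simple" t-test and variance analysis. It then proposes a difference-in-difference (DID) design, with propensity score matching as the second choice. The note under Table 2 lets the table's cells hold secondary as well as primary outcome indicators. The third arm is 200 participants who receive counselling and no product.

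**The concern.** A side effect of a product can be recorded only for someone who was given the product, and only after the participant or interviewer has decided that the product caused the symptom. The counselling arm has no study product, so as worded this item is empty there by construction. In the other two arms the attribution is made with full knowledge that a product was supplied.

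Two errors follow, in opposite directions. Symptoms that smokers have anyway, or that come with withdrawal, may be credited to the product while the same symptoms in the counselling arm go unasked. Events in the product arms that are judged unrelated may be left out of the side-effect item. The trial means to inform policy on these products, so an excess of events over counselling, or the absence of one, is a result readers will want. It would be hard to interpret if the arms were asked different questions.

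**Working it through.** **Step 1. Set the collection text against the analysis text.**

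| Element | Product arms | Counselling arm |
|---|---|---|
| Side-effect item (Study design, Survey instrument) | Applies, after attribution to a product | No product to attribute to |
| Tracking of physical or mental health at visits (Study design) | Applies | Plausible, since the visits follow counselling that all arms receive; the reference to a user leaves it unclear |
| Health status (baseline survey, questionnaire) | Applies | Nothing excludes this arm |

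The side-effect item is listed separately from health in both places, so the product arms are asked something additional.

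**Step 2. Put the side-effect item into Table 2.** Before the intervention there is no study product, so a = 0 and b = 0. In the comparison group there is none at follow-up, so d = 0. The printed estimator is (d − b) − (c − a) = (0 − 0) − (c − 0) = −c. In absolute size this is the crude product-arm rate with nothing subtracted. The item does not suit that method.

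**Step 3. Size of the distortion.** The article gives no event rate to reproduce, so the rates here are assumptions. Let the true rate r be the same in a product arm and the counselling arm, with 200 per arm. Let recording be complete in the product arm, and let a fraction f of events be recorded in the counselling arm. Then:

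- Spurious risk difference: D = r − f·r = r(1 − f).
- With q = f·r and m = (r + q)/2, SE0 = √[2m(1 − m)/200] and SE1 = √{[r(1 − r) + q(1 − q)]/200}.
- Chance of a false significant result at two-sided 0.05 ≈ Φ[(D − 1.96·SE0)/SE1].

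Example with r = 0.20 and f = 0.50: q = 0.10, D = 0.10, m = 0.15. SE0 = √(2 × 0.15 × 0.85/200) = 0.0357 and SE1 = √[(0.16 + 0.09)/200] = 0.0354. The argument is (0.10 − 0.0700)/0.0354 = 0.85, so the chance is about 80%.

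| Recorded in counselling arm | r = 10% | r = 20% | r = 30% |
|---|---|---|---|
| 100% | 0 points; 5% | 0 points; 5% | 0 points; 5% |
| 75% | 2.5 points; 14% | 5 points; 26% | 7.5 points; 40% |
| 50% | 5 points; 48% | 10 points; 80% | 15 points; 95% |
| 0% | 10 points; above 99% | 20 points; above 99% | 30 points; above 99% |

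Each cell gives the spurious difference and then the chance of a false positive. In the first row, 5% is the nominal error rate. The table covers under-recording in the counselling arm only. Losses in the product arms through attribution would pull the other way and are not modelled.

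**The case against.** The strongest reply is that the visit sentence has two parts, and the first needs no attribution. Cough, headache, or a change in sleep or mood are alterations in physical or mental health, so they could be recorded in any arm. The visits follow counselling that every arm receives, health status is taken at baseline and in the questionnaire, and all participants complete the week-60 survey. No text leaves the counselling arm out.

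This stands, and it limits the point. A reader might infer that the counselling arm has no safety record, so that no valid comparator exists. The article does not support that: a partial record is plausible and only its extent is unclear. A reader might likewise take the bottom row of the table as the expected bias. That row assumes that nothing at all is recorded in the counselling arm, which the article does not state.

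It can also be said that no between-arm test of adverse events is announced, and that a summary of product tolerability among users is legitimate. Both are true. Still, apart from descriptive summaries and associations, the methods in Statistical analysis are between-group, they may be applied to secondary outcomes, and adverse events are listed under that heading.

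Finally, the form, checklist and definitions may sit in the full protocol, and the participant schedule figure is not shown. Their absence here is no fault. What remains is the collection wording that is stated: in both places the event-specific item is defined by attribution to a product.

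**Conclusion.** The point holds as a risk of differential ascertainment. The only event-specific item described cannot be answered by 200 of the 600 participants and depends on attribution made with knowledge of the arm. General health tracking may fill part of the gap, but its coverage of the counselling arm is not clear, and the product arms keep an extra prompt.

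The size is conditional. At assumed true rates of 10% to 30% in both arms and 200 per arm, the spurious difference runs from 0 with complete recording in the counselling arm, through 2.5 to 7.5 points at 75% and 5 to 15 points at 50%, to 10 to 30 points in the extreme of no recording. Neither the event rates nor the recording fraction comes from the article. The bias arises only if events are compared between arms; a descriptive account within the product arms is not affected by the missing comparator. The change is worth making before data collection, because unequal questioning cannot be repaired in the analysis.

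**What to change.** In Study design and Survey instrument, state that the same adverse-event questions are put to all three arms at every scheduled follow-up (weeks 12, 24, 36, 48 and 60), whatever the suspected cause. Make attribution to a product a separate item, answered after the event has been recorded. Say explicitly that the health tracking at visits covers the counselling arm.

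In Secondary outcomes or Statistical analysis, state that events are compared by randomised arm, each product arm against counselling, for example as risk differences with confidence intervals. Report product-attributed side effects only descriptively, within the two product arms.

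The visits and the questionnaire are already planned. The cost is a wording change and some questionnaire items, a few more minutes per visit, and more recorded events to process.

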**Fig. 1 Fig1:**
[figure not shown]
Consolidated Standards of Reporting Trial flow chart

**Fig. 2 Fig2:**
[figure not shown]
Participant study schedule and SPIRIT checklist

#### Primary outcomes

The primary outcome will be long-term change in health status. The best proxy indication for demonstrating a reduction in toxin intake from tobacco smoking that is adequate to result in a clinically relevant long-term health benefit is unknown [59]. In the absence of more accurate health indicators, the change in smoking rate from baseline and the smoking cessation will be the primary outcomes. This study will evaluate the impact of e-cigarettes and nicotine pouches on cigarettes per day (CPD and smoking cessation (7-day point abstinence) at weeks 24 and 48 (the study period ends in 60 weeks. At 48 weeks, ARI will be ending the provision of the interventions). Self-reported point-prevalence abstinence in the previous week with biochemical validation will be exhaled carbon monoxide less than 10 parts per million (PPM).

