#### Sampling strategy and sample selection

Keeping in view the study objectives, the process of deciding the number of observations/sample respondents would be made through the determination of sample size, which is based on the extent and intensity of variation and heterogeneity in the subject population. For a population with lower variation, a small sample is adequate and vice versa, ceteris paribus. In empirical studies aimed at representing the salient features of the population under study, the sample size is important. Before calculating the sample size, a few details about the target population, including its size, variance, margin of error, and desired level of confidence in empirical estimates of important variables, are required [56]. A major constraint in arriving at the ideal sample size is the lack of adequate information and data regarding the standard deviation of variables/indicators. In the absence of this specific information, this study referenced international studies conducted in a similar design, although some variations were noted. To prevent bias, the study opted for the most suitable sampling method considering the budget constraints and local limitations related to variations in the target population. The study employed the equivalence trial formula to estimate the primary outcome, which focused on reducing the use of combustible cigarettes through the provided interventions (Table 1).$${n}_1={\left({Z}_{1-\frac{\alpha }{2}}+{Z}_{1-\beta}\right)}^2\ \frac{p_1\left(1-{p}_1\right)+{p}_2\left(1-{p}_2\right)}{{\left({p}_1-{p}_2\right)}^2}$$where$${p}_1= Proportion\ of\ outcome\ from\ group-1$$$${p}_2= Proportion\ of\ outcome\ from\ group-2$$$$\alpha = Level\ of\ significance$$$$1-\beta = Power\ of\ test$$$${Z}_{1-\alpha /2}=Z\ value\ of\ corresponding\ level\ of\ significance$$$${Z}_{1-\beta }=Z\ value\ of\ corresponding\ level\ of\ power$$$${n}_1= Sample\ size\ for\ one\ group$$

**Table 1 Tab1:** Sample size calculation based on previous studies

Indicators	Information	Study: Hajek et al. (2019) [50]	Study: Smith et al. (2022) [12]	Study: Rigotti et al. (2018) [14]	Study: Caponnetto et al. (2013) [16]
	Rounded figures				
Proportion of outcome from group 1 (p1)	0.18	18%	26%	10%	14%
Proportion of outcome from group 2 (P2)	0.09	9%	6%	26%	5%
Level of significance (alpha)	0.05				
Power (1-beta)	0.8				
Z alpha	1.96				
Z beta	0.84				
Sample size group 1 (n1)	222.1	222	49	86	163

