Based on the aforementioned formulas, from Hajek et al. [50], Smith et al. [12], Rigotti et al. [14], and Caponnetto et al. [16] derived 222, 49, 86, and 163 for single group respectively. According to acceptable norms and standards, the selected sample should represent the population. By the safe decision and following the abovementioned procedure, this study proposes a sample size of 600 participants, which will be randomly divided into three groups as follows:E-cigarette: The 200 participants will receive e-cigarettes along with basic care counselling.Nicotine pouches: The 200 participants will receive nicotine pouches along with basic care counselling.Basic care counselling: The 200 participants will receive basic care counselling.

Under the Lead Researcher [name], ARI team will conduct interview of participants and assign and unique ID to each potential participant at the screening stage. After that, the lead research Dr. [name] will generate the allocation sequence and will assign participants to interventions by using STATA software for the randomization.

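### No decisive primary outcome: CPD change and 7-day abstinence are co-equal at weeks 24 and 48 for two products, and the same abstinence measure is also listed as secondary

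*Protocol article*

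**What the plan says.** Four places in the protocol article bear on this.

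- **Primary outcomes, opening.** "The primary outcome will be long-term change in health status". The section then says that the best proxy for a long-term health benefit is not known, and substitutes two measures: "the change in smoking rate from baseline and the smoking cessation will be the primary outcomes".
- **Primary outcomes, timing and validation.** The effect of e-cigarettes and nicotine pouches is to be evaluated "on cigarettes per day (CPD and smoking cessation (7-day point abstinence) at weeks 24 and 48". The exhaled CO threshold (below 10 ppm) is attached to abstinence. No verification is stated for CPD.
- **Secondary outcomes.** "Secondary outcomes will include 7-day point-prevalence abstinence (at all subsequent checkups; biochemically validated at weeks 12, 24, 36, 48, and 60".
- **Sampling strategy and sample selection.** This section speaks of one "primary outcome, which focused on reducing the use of combustible cigarettes through the provided interventions". Table 1 sizes a comparison of two proportions, 18% vs 9%, with alpha 0.05 (Z 1.96) and power 0.8. Then "this study proposes a sample size of 600 participants, which will be randomly divided into three groups as follows", at 200 per arm.

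On the analysis, the Statistical analysis section says: "The differences in intervention indicators between the control and the treatment groups will be evaluated". The methods are the t-test and variance analysis, with difference-in-difference or propensity score matching for the treatment effect.

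**The concern.** The article ranks no outcome, week or product first, and no rule says whether one success is enough or all must succeed. The same endpoint at the same two weeks is both primary and secondary. The sizing describes a trial with one primary comparison, which the Primary outcomes section does not define.

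Three things are at stake. First, several different results could be reported as a positive primary result. Second, the stated 5% error and 80% power describe a single test of proportions, and the CPD outcome has no sizing at all. Third, CPD ranks equally with CO-verified abstinence. The control arm receives counselling only (Study design), so participants know whether they were given a product. An outcome without stated verification, reported by people who know their arm, could carry the conclusion alone.

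**Working it through.** **1. The plan's own figure.** The formula in the Sampling strategy section is n = (Zα + Zβ)² × [p1(1−p1) + p2(1−p2)] / (p1−p2)². With p1 = 0.18 and p2 = 0.09:

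(1.96 + 0.84)² × (0.1476 + 0.0819) / 0.0081 = 7.84 × 28.33 = 222.1, as in Table 1.

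The other three columns give 48.8, 86.5 and 162.5, against 49, 86 and 163. The sizing reproduces, and it is for one two-group comparison at an unsplit alpha.

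**2. Number of primary comparisons.** 2 outcomes × 2 weeks × 2 products against counselling = 8. Health status is not counted, because the section replaces it with the two proxies.

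**3. Chance of at least one false positive if each of the 8 is tested at two-sided 0.05.** If all were independent: 1 − 0.95⁸ = 33.7%. They are not independent. With equal arms and a shared control, the two product comparisons correlate at 0.5. The correlations between outcomes and between weeks are not in the article, so they are assumed and varied. The figures below come from simulating 8 correlated z-statistics (1 million draws), using the same value for the outcome and the week correlation and multiplying the two where both differ.

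| Assumed correlation | 8 tests, either direction | 8 tests, favouring a product | One product (4 tests), either direction |
|---|---|---|---|
| 0 | 31.6% | 16.9% | 18.5% |
| 0.5 | 27.8% | 14.1% | 16.2% |
| 0.7 | 23.8% | 11.9% | 13.7% |
| 0.9 | 17.3% | 8.7% | 9.8% |

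If every pair of the four results within a product comparison correlates at 0.9, the last row becomes 16.5%, 8.3% and 9.3%. For a single test the nominal values are 5% in either direction and 2.5% favouring the product.

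**4. One outcome at one week.** Two product comparisons remain. At 0.05 each, with the shared control, the chance of at least one false positive is 9.1% (1 − 0.95² = 9.75% if independent).

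**5. Power with 200 per arm, 18% vs 9%.** The standard error is √(0.2295/200) = 0.0339, so 0.09/0.0339 = 2.66.

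- At 0.05: Φ(2.66 − 1.96) ≈ 76%.
- At 0.025 (first Holm step): Φ(2.66 − 2.24) ≈ 66%. Reaching 80% at 0.025 would take about 270 per arm.

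A pooled-variance calculation gives 75% and 65%.

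**The case against.** The strongest reply is that the article never says each test is run at 0.05 or that one success suffices. Its only alpha is a Table 1 input. Splitting alpha and ordering tests are commonly left to a statistical analysis plan, which is not shown. A reader might infer from the article that the trial has a false-positive rate of a quarter or more, or that a multiplicity correction has been omitted. The documents support neither. The percentages follow only if all eight comparisons are tested at 0.05, they depend on correlations that the article does not give, and they count errors in both directions. The rate for a false result favouring a product is about half as large.

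The count of eight can also be questioned. Variance analysis could mean a three-arm omnibus test. Two different products can be read as two separate questions that share a control, so a joint error rate is a choice. No comparison of one product with the other is named as primary, so none is counted here.

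On health status, the section presents the two smoking measures as stand-ins and says why. That is awkward wording with a disclosed limitation rather than a third competing test. The secondary listing might be meant as the full series of visits, with weeks 24 and 48 singled out as primary, but the text does not say so.

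All of this limits the size of the problem. It does not remove the core of it. An analysis plan can allocate alpha only after the protocol has said which outcome and week are primary. Here the protocol names several as equals and gives one of them two ranks.

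**Conclusion.** The point holds as a fault in what the article fixes: joint primary outcomes with no decisive outcome or week, the same validated abstinence measure at weeks 24 and 48 in both the primary and the secondary list, and a sample size for one comparison of proportions.

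If the eight comparisons were each tested at two-sided 0.05, the chance of at least one false positive would be about 17-32% in either direction, about 9-17% in favour of a product, and about 10-19% within one product. These ranges rest on the assumed 0.05 per test and on assumed outcome and week correlations of 0.9 down to 0. They illustrate the room left open. They are not the trial's stated error rate. Even the lowest value in each range is well above the nominal rate for one test.

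**What to change.** - **Primary outcomes.** Name one primary outcome: CO-verified 7-day abstinence at week 48. It is a proportion, as in the sizing, and it is verified. It is not an exact match: the Empirical review describes the trial behind 18% vs 9% as measuring sustained one-year abstinence, for e-cigarettes against nicotine replacement therapy.
- **Secondary outcomes.** Move CPD and week-24 abstinence here, and list each outcome and week under one rank only.
- **Health status.** Describe it as the underlying aim, not as a primary outcome.
- **Sampling strategy.** Say that the calculation is for this outcome, so that the wording about reduced cigarette use no longer points elsewhere.
- **Two products.** State whether the two comparisons with counselling are separate questions at 0.05 each (joint error about 9.1%) or share 0.05, for example by Holm.

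The article says recruitment has not started, so the change is one of wording, with the trial registration to be checked for agreement. The cost falls on power if alpha is shared: about 66% at the first Holm step for 18% vs 9% with 200 per arm, against about 76% at 0.05. The latter is already below the planned 80%, because Table 1 asks for 222 per arm.

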#### E-cigarettes with NRT intervention

A randomized trial of e-cigarettes for quitting smoking conducted by a study [49] used a three-arm design — e-cigarettes with nicotine, nicotine patches, and placebo e-cigarettes. The criteria for eligibility included at least 18 years old, smoking 10 or more cigarettes per day (CPD) for the previous year, wanting to quit, and being able to give consent. The main result was quitting smoking for seven days. The follow-up periods were 1, 3, and 6 months. The treatment and the control groups were compared with multivariate regression adjustment and the *χ*^2^ test. According to the findings, e-cigarettes, whether they included nicotine or not, were only slightly more efficient than nicotine patches at aiding smokers in quitting. A few negative side effects were also noticed. E-cigarettes’ role in tobacco control was found to be unclear, with additional research recommended to clarify their overall advantages and disadvantages, both for individuals and for populations.

To determine the effectiveness of e-cigarettes and NRT for smoking cessation, another study [50] conducted a two-group pragmatics multicenter RCTs. The first group received nicotine replacement treatment, while the second group was given cigarettes. To examine the effects of e-cigarettes and NRT, a total of 884 subjects were analyzed using follow-up technique. The primary objective was sustained abstinence for 1 year. It was confirmed biochemically and assessed using a mixed-method analysis with binary regression and the generalized linear method (GLM), while secondary outcomes included participant-reported treatment use and respiratory symptoms. E-cigarettes were found to be more effective method of quitting smoking compared to NRT. Lee et al. [10] conducted a two-arm, single-center RCT to examine the efficacy of e-cigarettes and NRT for smoking reduction and cessation. Male adults over 18 who had smoked for at least 3 years and who were motivated to quit smoking altogether or cut back on their cigarette intake were qualified as eligible subjects if they had smoked at least 10 CPD in the year prior.

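### The planning rates of 18% and 9% are described as one-year sustained abstinence, the cessation outcome is 7-day point prevalence, and no outcome links abstinence across visits

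*Protocol article*

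**What the plan says.** Under Primary outcomes, the article opens with "The primary outcome will be long-term change in health status". It says the best proxy for a health benefit is unknown, and puts change in smoking rate and cessation in its place. Cessation is "smoking cessation (7-day point abstinence) at weeks 24 and 48", with validation stated as "Self-reported point-prevalence abstinence in the previous week with biochemical validation will be exhaled carbon monoxide less than 10 parts per million".

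Under Secondary outcomes, the same measure returns: "7-day point-prevalence abstinence (at all subsequent checkups; biochemically validated at weeks 12, 24, 36, 48, and 60". Neither section contains an outcome that depends on more than one visit.

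Table 1, under Sampling strategy and sample selection, is titled "Sample size calculation based on previous studies". Its adopted column sets "Proportion of outcome from group 1 (p1)" at 0.18 and "Proportion of outcome from group 2 (P2)" at 0.09, the same figures as in the reference 50 column. With significance level 0.05 and power 0.8 it gives 222.1 per group. The literature review (E-cigarettes with NRT intervention) says of reference 50: "The primary objective was sustained abstinence for 1 year", confirmed biochemically. The text above Table 1 describes the sized outcome in a third way, as a reduction in combustible cigarette use. The trial will randomise 600 participants, 200 per arm.

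**The concern.** A sample-size calculation justifies a trial only for the outcome whose rates went into it. One-year sustained abstinence and abstinence in the week before a visit are different events. They can have different control rates and different treatment effects. If 18% and 9% belong to the first and the trial measures the second, the stated power is not the power of the planned comparison.

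The second issue is what the outcomes can show. Each visit is judged alone. A participant who stops before week 24, relapses, and stops again before week 48 is a quitter at both primary visits, exactly like one who never smoked in between. The protocol wants to inform policy on these products as cessation aids, so readers will ask how many people stayed abstinent. As written, no outcome answers that, although the readings for a partial answer will be collected.

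**Working it through.** **1. Reproduce Table 1.** The article's formula is n = (1.96 + 0.84)² × [p1(1−p1) + p2(1−p2)] / (p1−p2)².

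For 0.18 and 0.09: 7.84 × (0.1476 + 0.0819) / 0.0081 = 7.84 × 0.2295 / 0.0081 = 222.13, against the stated 222.1. The other three columns give 48.76, 86.48 and 162.51, against 49, 86 and 163. The arithmetic is correct.

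**2. Set the endpoints side by side.**
- Reference 50, source of the adopted rates: one-year sustained abstinence, biochemically confirmed.
- This trial, primary: 7-day abstinence with CO below 10 ppm, at weeks 24 and 48 separately.
- This trial, secondary: the same 7-day measure at weeks 12, 24, 36, 48 and 60.
- Reference 12, another Table 1 source: reduction in intake of at least 50% at 6 months, with sustained abstinence at 6 months as secondary.
- Reference 14, another Table 1 source: validated abstinence at 6 months.

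The adopted rates do not belong to the outcome measured.

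**3. Power at 200 per arm for the adopted rates, two-sided 0.05.** The standard error is √(0.2295/200) = 0.0339. Then 0.09/0.0339 − 1.96 ≈ 0.697, which gives a power of 75.7%. With a pooled variance under the null it is 75.2%. Reaching 80% takes 222 per arm, or 3 × 222 = 666 in total before any dropout.

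**4. Power for 7-day point prevalence.** The documents give no rates for it. The control rates below are assumptions, used only to see whether the direction can be fixed. The odds ratio implied by 18% and 9% is (0.18/0.82)/(0.09/0.91) = 2.22.

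| Assumed control rate | Same 9-point difference: n per arm, power at 200 | Same odds ratio 2.22: n per arm, power at 200 |
|---|---|---|
| 14% | 288, 64.6% | 157, 88.5% |
| 18% | 334, 58.2% | 132, 93.1% |
| 25% | 399, 50.9% | 110, 96.5% |

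If the absolute difference carries over, power falls below the 75.7% of step 3. If the odds ratio carries over, power rises above it. These figures are not bounds: a 6-point difference on 14% would give 36.0%.

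**5. What the visit data allow.** Visits are 12 weeks apart, and each reading asks about 7 of those 84 days (8.3%). This is the share of time observed. It does not say how often status is misjudged. Validated status at weeks 24, 36, 48 and 60 is already planned, so a variable requiring abstinence at every one of them can be derived without new measurement.

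**The case against.** Seven-day point prevalence is a legitimate endpoint. The article's own review describes several cessation trials that used it as their main outcome. It applies equally to all arms, and no bias between arms is shown. This stands, and it is why the primary cessation outcome need not be replaced.

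A reader might infer that a long-term claim goes untested. The text does not support that. The long-term wording under Primary outcomes is about health status, which sustained abstinence would not measure directly either. The abstract's Discussion speaks of short- and medium-term effects. Week 60 supplies a validated reading 12 weeks after product supply ends.

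A reader might also take 7 of 84 days as a misclassification rate, or conclude that the mismatch leaves the trial underpowered. Neither follows: the fraction is only a recall window, and step 4 shows that power could move either way.

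Table 1 draws on four studies, and at least two of the other three are not described as one-year sustained abstinence. That is true, but the adopted 0.18 and 0.09 coincide with reference 50 alone. The article also says it will enrol more than the optimum sample, but gives no number and fixes the arms at 200.

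Finally, abstinence at several visits is still repeated point prevalence. A participant could smoke between visits and qualify. This stands and limits what the added outcome may be called. It also means that 18% and 9% cannot be assigned to it.

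**Conclusion.** The point holds in two parts. First, the 222 per group and 80% power rest on rates that the protocol itself ties to one-year sustained abstinence, whereas cessation is measured as 7-day point prevalence. The power of the planned comparison cannot be derived from the documents. Across the scenarios tabulated above it runs from about 51% to 97%, and those control rates are assumptions. Even for the adopted rates, 200 per arm gives about 75–76%, assuming a two-sided 0.05 test of one pair of arms and no dropout.

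Second, no outcome requires abstinence across visits, so persistent quitting is not distinguished from intermittent abstinence despite five planned validated readings. This is a gap in what the trial can conclude and does not invalidate its primary outcome. Both parts warrant a change before the analysis is fixed.

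**What to change.** 1. Keep 7-day point prevalence with CO below 10 ppm as the primary cessation outcome.
2. Add a key secondary outcome: validated 7-day abstinence at every one of weeks 24, 36 and 48, and a version that also requires week 60 to show durability. Count a missed or unvalidated visit as not abstinent.
3. Call this repeated point prevalence, unless the existing questionnaire includes a question on smoking since the last visit. Rest any statement about lasting cessation on this outcome.
4. In Sampling strategy and sample selection, state that 18% and 9% are one-year sustained-abstinence rates and not rates for 7-day point prevalence, and that even for those rates 200 per arm gives about 75–76% power, not 80%.

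The cost is outcome wording, a derived variable, a few sentences on sample size and, if chosen, one questionnaire item. No new visit or CO test is needed. The downside is lower quit rates and less power on the stricter outcome. As an illustration with assumed rates that keep the twofold ratio, 14% against 7% has about 63% power at 200 per arm, and 10% against 5% about 48%.
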